### 2.12. Randomization and allocation concealment

After recruitment, patients who meet the eligibility criteria would be randomly and equally divided into 2 groups at a ratio of 1:1 with computer-based random sequence. Each subject will be registered with a unique ID. After screening and informed consent forms obtaining, subjects will be assigned to experimental group (conventional treatments plus *Panax notoginseng [Sanqi]*), control group (conventional treatments) randomly. Allocation was concealed in opaque envelopes until the beginning of intervention. Each subject will receive different medications, whereas all subjects will be aware of the group.

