## 2. Methods/design

### 2.1. Study design

This is a prospective 2-center, assessor and statistician blinded, randomized, controlled trial with a parallel 2-arm group from June 2021 to May 2023. This study protocol is draw up based on Recommendations for Interventional Trials (SPIRIT) 2013 statement.^[10]^ The SPIRIT checklist will be presented in (Table S1, Supplemental Digital Content, http://links.lww.com/MD/H991). A total of 106 participants will be randomized into 2 groups at a ratio of 1:1. Participants in the treatment group will be treated with conventional treatments plus *Panax notoginseng (Sanqi*). Participants in the control group will be treated with conventional treatments.

The whole study period is 35 days, including 5-days baseline observation, 30-days treatment. Subjects will be measured with the platelet aggregation rate and serum TLR4, MyD88, NF-*κ*B, COX-2, IL-6, CRP, TXB2 level for clinical efficacy and mechanisms at baseline and the 14^th^, 30^th^ day of treatment. (Fig. 1, Table 1).

**Table 1 T1:** Schedule of enrollment, interventions and assessments.

Study procedure	Study period		
	Enrollment（d）	treatment period （d）	
Timepoints	-5^th^-0d	14^th^d ± 1d	30^th^d ± 1d
Enrolment			
Demographics	X		
Vital signs	X		
Medical history	X		
Complications	X		
Eligibility screen	X		
PHQ-9	X		
GAD-7	X		
MMSE	X		
Informed consent	X		
Random allocation	X		
Interventions			
Conventional treatments + Panax notoginseng		X	X
Conventional treatments		X	X
Assessments			
Platelet aggregation rate	X	X	X
TLR4, MyD88, NF-*κ*B, COX-2, IL-6, CRP, TXB2	X	X	X
Coagulation function	X	X	X
Safety evaluations	X	X	X
Patient compliance	X		
Drug combinations	X		
Adverse events	X		
Research summary	X		
Review statements	X		

GAD = generalized anxiety disorder, MMSE = mini-mental state examination, PHQ = patient health questionnaire.

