### 2.5. *Study group*

106 participants who meet above-mentioned criteria with signed informed consents will be selected. The subjects will be randomly divided into 2 groups in a 1:1 ratio, namely the experimental group and control group, 53 cases in each group.

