### 2.13. Statistical analysis

Data analysis will be based on the full analysis set and per-protocol set in the light of data missingness (last-observation-carried-forward [LOCF] method) and robustness of our analytical results. All data will be analyzed using IBM SPSS Statistics 21.0 (v21.0, IBM Corp., Armonk, NY). Descriptive statistics will be performed with means ± standard deviations or median [interquartile range]. Baseline characteristics of patients will be summarized by groups and compared with Chi-square for categorical variables, and Student’s independent *t* test or nonparametric Mann-Whitney U test for the continuous variables. Primary and secondary outcomes are applicable to 2-way repeated measures Anova, and Post Hoc test will be for multiple comparisons between groups and time-points. If there is a violation of distribution assumption, appropriate transformation will be used. A *P* value < 2- sided 0.05 will be considered as significant.

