#### 2.13.1.
*Primary outcomes*.

Platelet aggregation rate, serum TLR4, MyD88, NF-*κ*B, COX-2, IL-6, CRP, TXB2 level as primary outcomes, which are tested at baseline, 14^th^ and 30^th^ day of treatment, will be analyzed with 2-way repeated measures Anova. A significant effect of group indicates that the platelet aggregation rate & TLR4/MyD88/NF-*κ*B signaling pathway associated proteins are different between groups after intervention.

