### 2.14.
*Quality control*

Reasons of dropouts during research periods will be fully recorded for data analysis. To ensure quality, the PI ([name]) and sub-PI ([name]) will verify all study process every 2 months and check data authenticity every 2 week on-site or online. Moreover, a third party, scientific research department of *Xi’an Hospital of Traditional Chinese Medicine (Xi’an Affiliated Hospital of Shaanxi Provincial Hospital of Chinese Medicine*), will be invited to manage the data independently.

Since this study mainly involves some objective indicators tested by device, measurement bias are mainly from different devices. In order to increase consistency, on the 1 hand, blood samples will be taken from patients at fixed time (7:30 am) by a fixed nurse. On the other hand, blood samples from the sub-center (*Shanxi Provincial Hospital of Chinese Medicine [Shaanxi Academy of Traditional Chinese Medicine]*) will be delivered to our hospital(*Xi’an Hospital of Traditional Chinese Medicine [Xi’an Affiliated Hospital of Shaanxi Provincial Hospital of Chinese Medicine]*) on the day for unified storage and detection. Moreover, record cards for all patients will be prepared for treatment history, including treatment date, personal information and their signatures.

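### The outcome models have no centre term in a two-centre trial where only one centre's blood is transported: a small, avoidable loss of precision

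*Protocol article*

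**What the plan says.** Section 2.1 describes the design: "This is a prospective 2-center, assessor and statistician blinded, randomized, controlled trial with a parallel 2-arm group". Section 2.4 names the two hospitals.

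On analysis, section 2.13 states: "Primary and secondary outcomes are applicable to 2-way repeated measures Anova, and Post Hoc test will be for multiple comparisons between groups and time-points". Sections 2.13.1 and 2.13.2 repeat this model for the primary outcomes and for coagulation. The two factors are group and time; centre appears in none of these sections. Section 2.13.1 also fixes how the result is read: "A significant effect of group indicates that the platelet aggregation rate" and the pathway proteins differ between the arms.

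On sample handling, section 2.14 has blood drawn at a fixed hour by a fixed nurse. Sub-centre samples go to the lead hospital "on the day for unified storage and detection". Lead-hospital samples need no such journey. The section names differing devices as the main source of measurement bias.

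On allocation, section 2.12 says that eligible patients "would be randomly and equally divided into 2 groups at a ratio of 1:1 with computer-based random sequence", and section 2.5 gives "53 cases in each group". Neither mentions centre, strata or blocks.

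**The concern.** The two centres may differ in case mix, in conventional treatment and in sample transport. Testing at one laboratory removes device differences but not these.

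A centre difference that is constant over time would cancel in a change from baseline or in the group-by-time interaction. It does not cancel in the between-subject group effect that 2.13.1 uses. There it has two consequences when centre is left out of the model:

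- The between-centre variance is added to the error against which the group effect is tested, so power falls.
- If the arms contain different shares of sub-centre patients by chance, the estimated group difference moves by that difference in share times the centre shift.

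At stake is some precision on a primary comparison planned at only 80% power.

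**Working it through.** **Inputs from the article (2.11, 2.5).** Difference 14 (it is not clear whether this means points or relative per cent), correlation 0.7, 3 time points, one-sided 0.05, 48 per group, 80% power, 53 per group recruited.

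**Assumed, because the article gives none of them.** Centre split, centre shift, and whether the planning SD is within-centre or total.

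**1. The plan's own figure.** No SD is stated, so 96 cannot be reproduced forwards. Solving backwards for the mean of each subject's three values:

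- d = (1.645 + 0.842)/√(48/2) = 0.51 SD
- SD of the subject mean, if 14 is in points: 14/0.5075 = 27.6
- SD at a single time point under compound symmetry: 27.6/√0.80 = 30.8, where 0.80 = (1 + 2×0.7)/3

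The attrition step is 96 × 1.10 = 105.6, rounded to 106 as stated.

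**2. Power lost by omitting centre, if the planning SD is within-centre.** Let p be the share of patients at one centre and c the centre shift in within-centre SDs of the subject mean. The variance inflates by v = 1 + p(1−p)c², and power = Φ(2.486/√v − 1.645).

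| c | v (p = 0.8 to 0.5) | Power (p = 0.8 to 0.5) |
|---|---|---|
| 0.25 | 1.01 to 1.02 | 79.7% to 79.5% |
| 0.5 | 1.04 to 1.06 | 78.6% to 77.9% |
| 1.0 | 1.16 to 1.25 | 74.7% to 71.9% |

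On this scale 0.5 SD is 0.5 × 27.6 = 13.8 points, about as large as the planned treatment difference.

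**3. Power gained by a centre term, if the planning SD is total.** Take 30 of 106 patients at the sub-centre and a 10-point shift.

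- Share of variance due to centre: 0.283 × 0.717 × 10²/27.6² = 20.3/761 = 2.7%
- Power with centre removed from the error: Φ(2.486/√0.973 − 1.645) = Φ(0.875) = 81%, against 80%

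**4. Chance imbalance, only if allocation is not stratified by centre.** Spreading 30 sub-centre patients at random over 53/53 (hypergeometric), the arms differ by 6 or more with probability 28% and by 10 or more with probability 5%. With the 10-point shift, the group difference moves by 6/53 × 10 = 1.1 points and 10/53 × 10 = 1.9 points. The standard error is 27.6 × √(2/53) = 5.4 points, so even the larger move is about a third of a standard error.

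**5. Type I error (simulation, 96 patients, equal centres, one-sided 5%).**

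| Allocation and model | c = 0.5 | c = 1.0 |
|---|---|---|
| Unstratified, no centre term | 5.4% | 5.0% |
| Stratified, no centre term | 4.7% | 3.5% |
| Stratified, centre term | 4.9% | 5.0% |

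With stratification and a centre term, power was 80.6% at c = 0.5 and 79.8% at c = 1.0.

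**The case against.** The model is valid without centre. Under proper randomisation the standard error already reflects chance imbalance in centre mix, and the simulated error rate stays near 5%. Section 2.14 also takes deliberate steps to make the centres alike. Section 2.9 defines the primary outcome as a change, in which a constant shift cancels. The gap between one-sided planning in 2.11 and two-sided testing in 2.13 costs far more: about 70% power at 48 per group.

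Most of this stands and limits the point to a minor one. It does not remove it. The analysis sections name a specific model with no place for centre, and 2.13.1 reads the group effect rather than the change.

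Three stronger readings are tempting, and the article does not support them:

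- **That allocation is one unstratified sequence.** Section 2.12 says neither. A condensed article commonly leaves strata and blocks to the full protocol, so the silence proves nothing. The wording on equal division, with a fixed 53 per arm, also does not describe simple coin-toss randomisation.
- **That transport biases the treatment comparison.** Nothing in the article shows that same-day delivery shifts the aggregation rate. If it does, the effect falls on both arms of the sub-centre.
- **That a centre term would gain several points of power.** That needs a larger centre share of variance than the 2.7% implied by a 10-point shift, and the article gives no basis for one.

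**Conclusion.** The primary and secondary models omit centre in a two-centre trial, and the effect chosen for interpretation is one in which a constant centre difference does not cancel. The consequence is lost precision and exposure to chance imbalance, with no systematic bias and no inflated error rate.

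The loss is small under moderate assumptions: power of about 78-79% instead of 80% at a 0.5 SD centre shift, or about 1 point gained from a centre term at a 10-point shift with 30 of 106 patients at the sub-centre. It reaches 5 to 8 points only if the centres differ by a full SD. Centre sizes, the centre shift, the nature of the planning SD and the unit of the 14 are all assumed. The point about the model is firm; the point about allocation is conditional on the full protocol. This is a minor, inexpensive improvement.

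**What to change.** In 2.13, and by reference in 2.13.1 and 2.13.2, state that the repeated measures model has group and centre as fixed between-subject factors and time as the within-subject factor. Centre should enter as a main effect, without a group-by-centre interaction. This costs one degree of freedom in the test of the group effect (94 to 93 error degrees of freedom at 96 patients) and no patients or procedures. It can be specified at any time before the analysis.

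In 2.12, state whether allocation is stratified by centre. If it is not, generate a separate blocked list for each centre for patients still to be randomised, at the cost of a second list and one sentence. The centre term is worth adding either way: it recovers precision without stratification, and with stratification it prevents the conservative test seen in the simulation.

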### 2.13. Statistical analysis

Data analysis will be based on the full analysis set and per-protocol set in the light of data missingness (last-observation-carried-forward [LOCF] method) and robustness of our analytical results. All data will be analyzed using IBM SPSS Statistics 21.0 (v21.0, IBM Corp., Armonk, NY). Descriptive statistics will be performed with means ± standard deviations or median [interquartile range]. Baseline characteristics of patients will be summarized by groups and compared with Chi-square for categorical variables, and Student’s independent *t* test or nonparametric Mann-Whitney U test for the continuous variables. Primary and secondary outcomes are applicable to 2-way repeated measures Anova, and Post Hoc test will be for multiple comparisons between groups and time-points. If there is a violation of distribution assumption, appropriate transformation will be used. A *P* value < 2- sided 0.05 will be considered as significant.

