### 2.3. Study population

#### 2.3.1.
*Inclusion criteria*.

1.Subjects, diagnosed with ischemic stroke, according to the *International Classification of Diseases (ICD-11, 8B11*),^[12]^ and *Chinese Guidelines for Diagnosis and Treatment of Acute Ischemic Stroke 2018*;^[13]^

2. Subjects, diagnosed with aspirin semi-resistance, according to 0.5 mmol/L arachidonic acid-induced mean platelet aggregation rate ≥ 20%, or 10*μ*mol/L adenosine diphosphate-induced mean platelet aggregation rate ≥ 70%;^[4,14]^

3. Subjects, aged between 45 and 65 years old, male or female;

4. Subjects, predicted in the low-risk profile of recurrent stroke, Essen stroke risk scores ≤ 3 points;^[15]^

5. Only taking single antiplatelet drug, not overlapping the use of activating blood and removing stasis herbs medicine;

6.Sign the informed consent forms.

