### 2.9. Primary outcomes

The primary outcome will be the change in platelet aggregation rate of elbow venous blood for platelet adhesion properties at baseline, 14^th^ day and 30^th^ day of treatment; Moreover, the serum TLR4, MyD88, NF-*κ*B, COX-2, IL-6, CRP, TXB2 level for AR improvement based on the TLR4/MyD88/NF-*κ*B signaling pathway would be also detected at above-mentioned 3 time points.

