### 2.11. Estimation of sample size

The study is powered for the primary outcome measure of platelet aggregation rate. The number of patients required for the study was computed a priori with software PASS 15.0.1, NCSS, LLC, America. The sample size calculation was based on the results of preliminary small sample pilot trial by our team, which showed a decrease of-14% in platelet aggregation rate in the exercise group compared with control group (autocorrelation coefficient 0.7, 3 time points). A 1-sided 0.05 level of significance and a sample size of 96 participants (48 per group) provided 80% statistical power to demonstrate this difference in platelet aggregation rate. To accommodate for a 10% attrition rate, we will recruit a total of 106 participants (53 per group) (PASS 15.0.1, 2-way repeated measures Anova; allocation ration = 1).

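### LOCF is the only missing-data method named; for patients lost before day 14 it enters the pre-treatment value as the outcome, which can bias the group difference by an amount that depends on when and in which arm patients leave

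*Protocol article*

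**What the plan says.** Section 2.13 ties the full analysis set and the per-protocol set to "data missingness (last-observation-carried-forward [LOCF] method) and robustness of our analytical results". No other handling of missing data appears. The analysis model is fixed in the same section: "Primary and secondary outcomes are applicable to 2-way repeated measures Anova".

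Section 2.9 defines the outcome: "The primary outcome will be the change in platelet aggregation rate". Section 2.13.1 adds the serum markers and gives the visits for all primary outcomes, "which are tested at baseline, 14^th^ and 30^th^ day of treatment".

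Entry under section 2.3.1 is by either of two cut-offs on aggregation: "arachidonic acid-induced mean platelet aggregation rate ≥ 20" per cent, or "adenosine diphosphate-induced mean platelet aggregation rate ≥ 70" per cent. Section 2.11 enlarges the sample with the words "To accommodate for a 10% attrition rate".

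Departure from the trial can be related to outcome and to arm. Section 2.3.3 lists serious adverse events, worsening of the stroke and receipt of under half the treatment among the withdrawal criteria. Section 2.8 counts severe stroke as dropout. Section 2.12 says that patients know their group.

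**The concern.** LOCF assumes that a patient's value stays where it was last seen. With two follow-up visits, that assumption has two forms. A patient lost between days 14 and 30 has a value taken on treatment carried forward, which may be close to the truth. A patient lost before day 14 has the baseline entered twice, so the analysis records no change for someone whose later values are unknown. In the treated arm this dilutes a real effect. If early loss differs between arms, it can also move the estimate when there is no effect.

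The named robustness analysis does not test this. A per-protocol set leaves patients out; it does not vary the assumption about their missing values. The result on the primary outcome could then depend partly on the pattern of departure, in a trial that patients know to be open and where only one arm takes an added product.

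**Working it through.** **The plan's own figures.** 96 × 1.1 = 105.6, which rounds to the stated 106. The 96 itself cannot be reproduced, because section 2.11 gives an effect ("which showed a decrease of-14% in platelet aggregation rate in the exercise group compared with control group") and a correlation of 0.7 but no SD. For a comparison at a single time with one-sided 0.05, 80% power and 48 per group, the implied SD is 14 / [(1.645 + 0.842) × √(2/48)] = 27.6 points. I use 15 and 27.6 as a range and read the 14% as percentage points.

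**Formula.** Let
- Δ be the true reduction at day 30;
- pT and pC be the fractions lost before day 14 in the treated and control arms, with loss unrelated to outcome within arm;
- r be the amount by which the mean baseline exceeds the mean at day 30 without any added effect.

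The expected reduction estimated under LOCF is

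(1 − pT) × Δ − (pT − pC) × r.

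The first term is dilution by zero-change values. The second is the effect of selecting high baselines, and it vanishes when early loss is equal.

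**Equal early loss.** This needs no assumed mean or SD.
- 10% per arm: 0.90 × 14 = 12.6.
- 20% per arm: 0.80 × 14 = 11.2.

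**Size of r.** Assume a population mean of 70, entry at 70 or above on a single agonist, and correlation 0.7. The selected baseline mean is 70 + 0.798 × SD, and the untreated day-30 mean is 70 + 0.7 × 0.798 × SD.
- SD 15: 82.0 against 78.4, so r = 3.6.
- SD 27.6: r = 0.3 × 0.798 × 27.6 = 6.6.

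**Unequal early loss.**

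| Early loss, treated / control | True Δ | LOCF, SD 15 | LOCF, SD 27.6 |
|---|---|---|---|
| 15% / 5% | 14 | 11.9 − 0.36 = 11.5 | 11.9 − 0.66 = 11.2 |
| 5% / 15% | 14 | 13.3 + 0.36 = 13.7 | 13.3 + 0.66 = 14.0 |
| 15% / 5% | 0 | −0.4 | −0.7 |
| 5% / 15% | 0 | +0.4 | +0.7 |

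Both patterns average 10% loss, the planned figure. Simulation with 53 per arm agrees: 11.5 and 11.3 in the first row, 13.7 and 13.95 in the second. An analysis of available data stayed at 14.0 to 14.1 throughout when Δ was 14.

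**Late loss.** If a fraction q of the treated arm leaves after day 14, the estimate changes by q × (effect at day 30 − effect at day 14). With a flat effect this is zero.

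**The planned group effect.** Averaged over three visits, with an effect of 14 at both follow-ups, it is (0 + 14 + 14)/3 = 9.3. With 10% equal early loss it becomes (0 + 12.6 + 12.6)/3 = 8.4. The proportional loss is the same 10%.

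**Standard error of the difference in change from baseline to day 30, 10% early loss per arm (simulation).**

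| SD | Δ | LOCF | Available data | LOCF lower by |
|---|---|---|---|---|
| 15 | 14 | 2.16 | 2.26 | 4% |
| 27.6 | 14 | 3.83 | 4.14 | 7% |
| 15 | 0 | 2.04 | 2.26 | 10% |
| 27.6 | 0 | 3.75 | 4.16 | 10% |

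The LOCF standard error nevertheless matches the simulated spread of the LOCF estimate (ratio 0.98 to 1.02). With Δ = 14, coverage of the 95% interval was 0.90 (SD 15) and 0.94 (SD 27.6) with 10% loss per arm, and 0.80 and 0.89 with 15% against 5%. That shortfall comes from bias.

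**The case against.** Four points on the other side carry weight.

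**Selection of high baselines.** A reader might infer that the entry cut-offs are the main source of bias, because carried baselines are too high. They are not. Regression to the mean affects both arms and cancels when early loss is equal. At 15% against 5% with SD 15, it accounts for 0.36 of the 2.46 points lost. Entry is by either agonist, so a patient selected on one need not be high on the other, and the serum markers have no cut-off at all. The single cut-off at 70 used above is a simplification.

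**Confidence interval.** A reader might also infer that LOCF makes the interval too narrow and inflates false positives. The simulations do not show this. The standard error is right for the LOCF estimator, and with no true effect the two-sided rejection rate stayed between 0.045 and 0.058. What stands is that the standard error ignores the information lost with the missing values.

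**Conditional bias.** The bias is not certain. Late loss with a flat effect, or equal loss with no effect, leaves essentially none. No passage gives dropout by arm; open treatment makes unequal loss possible, not established.

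**Use of LOCF.** A repeated measures ANOVA needs complete rows, so a filling rule keeps patients in the analysis. Also, the article does not define its full analysis set. If that set required a follow-up value, baselines would not be carried, but early losses would then be left out altogether. An unseen analysis plan may settle this, yet the choice of LOCF is stated here and is open to comment.

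**Conclusion.** The point holds in this conditional form: LOCF is fixed as the only missing-data method, and it can bias the group difference when patients leave before day 14. At the planned 10% attrition, all early and equal, a 14-point difference at day 30 falls to 12.6, a loss of 1.4 points. With the same total split 15% treated and 5% control it falls to about 11.2 to 11.5. With no true effect, such a split creates a spurious difference of about 0.4 to 0.7 points. The direction depends on timing and arm, and in the favourable cases named above there is essentially no bias.

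The lower standard error, 4 to 10% below the available-data value, is a second and smaller defect.

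The 12.6 rests on the article's 14 and 10%, on early timing, and on baselines being carried in the full analysis set. The remaining figures also rest on an assumed mean, SD, correlation structure, and dropout split that the article does not give. This should be changed, but it does not threaten the trial.

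**What to change.** In section 2.13, replace LOCF in the full-analysis-set analysis with a likelihood-based mixed model for repeated measures. It should use all observed day-14 and day-30 values, with group, visit and their interaction, adjust for baseline, and use no single imputation. LOCF may stay as a sensitivity analysis, labelled as such.

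The model is unbiased if missingness depends only on observed data. The withdrawal rules make that an assumption rather than a fact, and checks on departures from it can be set out in the analysis plan.

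The cost is a change of wording and a little programming; the MIXED procedure in the named software can fit the model. No new data or patients are needed. The interval will be slightly wider than under LOCF, because it reflects the information that was lost.

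### Platelet aggregation rate: no visit is decisive, the stated group-effect test averages in baseline and does not test change, and post hoc contrasts at 0.05 are not made subordinate to it

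*Protocol article*

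**What the plan says.** Section 2.9 defines the primary outcome as "the change in platelet aggregation rate of elbow venous blood for platelet adhesion properties at baseline, 14^th^ day and 30^th^ day of treatment". Three time points are listed and none is singled out.

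Section 2.13 analyses primary and secondary outcomes by two-way repeated measures ANOVA and adds: "Post Hoc test will be for multiple comparisons between groups and time-points". The threshold is common to all tests: "A *P* value < 2- sided 0.05 will be considered as significant". The Abstract also lists the ANOVA and the post hoc test side by side for the primary and secondary outcomes.

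Section 2.13.1 is the only place that says what a result would mean: "A significant effect of group indicates that the platelet aggregation rate" and the pathway proteins differ between the arms once treatment has been given. It does not mention the group-by-time interaction or the status of the post hoc tests.

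Section 2.11 powers the trial on platelet aggregation rate with the same ANOVA, three time points and an autocorrelation of 0.7. It uses "A 1-sided 0.05 level of significance", and "a sample size of 96 participants (48 per group) provided 80% statistical power".

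**The concern.** Three parts of the plan point to different tests of one outcome. Section 2.9 speaks of change, which in a group-by-time ANOVA is carried by the interaction or by visit-specific contrasts that take account of baseline. Section 2.13.1 relies on the group main effect, a difference in average level over all three visits, one of them before treatment. Section 2.13 adds visit-by-visit comparisons at the same threshold and does not say how they relate to the group effect.

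Two things are at stake. First, the effect that 2.13.1 interprets is diluted: with randomised arms the expected baseline difference is zero, so a real on-treatment effect is averaged with nothing. Second, the group effect, day 14 and day 30 answer different questions (average level, early effect, end-of-treatment effect) and can disagree in the same data. The plan does not say which one governs when they do. This would remain if platelet aggregation rate were the only primary outcome, so it is separate from the number of biomarkers listed as primary.

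**Working it through.** **Inputs.** From 2.11: 48 evaluable per group, three time points, correlation 0.7, 1-sided 0.05, 80% power, a 14% difference. From 2.13: 2-sided 0.05. No SD is given, and 14% is not identified as points or relative. Assumed here: the effect sizes in SD units, the correlation pattern (compound symmetric or AR(1)), and no adjustment of the post hoc tests.

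**1. The plan's own figure.** Without an SD, 48 per group cannot be reproduced; it can only be solved backwards. Under compound symmetry the variance factor of a three-visit mean is (1 + 2×0.7)/3 = 0.8. If 14% means points:
- group effect over three visits: SD = 14 / [(1.645 + 0.842) × √(2×0.8/48)] = 30.8 points
- single visit: SD = 14 / [(1.645 + 0.842) × √(2/48)] = 27.6 points

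Section 2.11 therefore does not show which contrast was sized.

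**2. What the group effect estimates.** With expected baseline difference 0 and the same effect d at days 14 and 30, it estimates (0 + d + d)/3 = 2d/3. A chance baseline imbalance enters with weight one third.

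**3. Power, assumed d = 0.5 SD, 2-sided 0.05, normal approximation, compound symmetry 0.7.**
- Group effect: 0.333/√(0.8×2/48) = 0.333/0.1826 = 1.826; Φ(1.826 − 1.960) ≈ 45%.
- Single visit, unadjusted for baseline: 0.5/√(2/48) = 0.5/0.2041 = 2.449; Φ(0.489) ≈ 69%.
- Day 30 adjusted for baseline, residual variance 1 − 0.7² = 0.51: 0.5/(0.2041×√0.51) = 3.430; Φ(1.470) ≈ 93%.

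If 0.7 is a lag-one AR(1) coefficient, the baseline–day 30 correlation is 0.7² = 0.49 and the variance factor of the mean is (3 + 2×(0.7 + 0.7 + 0.49))/9 = 0.753.
- Group effect: 0.333/√(0.753×2/48) = 1.881; about 47%.
- Adjusted day 30: 0.5/(0.2041×√(1 − 0.49²)) = 2.810; about 80%.

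The gap narrows but keeps its direction.

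The same dilution can be put on the plan's own terms. If 48 per group was sized for the full difference at all three visits, the design signal is 1.645 + 0.842 = 2.487. With equal baselines it is 2.487×2/3 = 1.658, and power is Φ(1.658 − 1.645) ≈ 51% at 1-sided 0.05 and Φ(1.658 − 1.960) ≈ 38% at 2-sided 0.05.

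**4. False-positive rate under no effect.** Monte Carlo, 40,000 trials per setting, 48 per group, each test at 2-sided 0.05, unadjusted:

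| What may count as success | Compound symmetric 0.7 | AR(1) 0.7 |
|---|---|---|
| Group effect only | 4.9% | 4.8% |
| Day 14 or day 30 | 8.3% | 8.0% |
| Group effect, day 14 or day 30 | 9.1% | 8.9% |
| Those plus the interaction | 12.9% | 13.0% |
| Those plus the baseline contrast | 14.3% | 14.7% |

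Day 14 or day 30 alone ranges from 7.1% (correlation 0.9) to 9.7% (correlation 0). Bonferroni on the two visits (0.025 each) brings that pair to 4.2%. If either ANOVA effect may also count at 0.05, the rate is still 10.4% (compound symmetric 0.7).

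**5. Disagreement between contrasts.** Illustration with an assumed fading effect, 0.5 SD at day 14 and 0.1 SD at day 30, AR(1) 0.7: significant in about 68% of trials at day 14, 8% at day 30 and 20% for the group effect.

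**The case against.** The strongest reply is that a criterion is stated. Section 2.13.1 ties the between-group conclusion to the group effect, 2.11 sizes the trial on the same ANOVA, and post hoc ordinarily means follow-up. On that reading platelet aggregation rate has one test and about 5% error, whatever the later comparisons show. A reader might infer that success can be claimed on whichever contrast reaches significance, so that the error rate simply is 8–14%. The documents do not support that. No section states an any-of rule, the interaction is nowhere named as a route to success, and wording about multiple comparisons may well denote an adjusted procedure that a full protocol or analysis plan would name. The choice of adjustment is ordinary SAP detail and is not counted here. The fading-effect example is also invented; it shows that contrasts can disagree, not that this trial would report the favourable one.

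The objection does not remove the mismatch in the stated text. The group effect includes baseline and is not the change that 2.9 makes primary. Section 2.13.1 says what a significant group effect indicates, but not that it alone decides or that post hoc contrasts cannot.

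It is also fair that a baseline-adjusted day-30 contrast replaces the stated test rather than clarifying it, so 2.11 has to follow. A single sentence making the post hoc tests supportive would settle the error rate, but would leave the diluted test in place.

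**Conclusion.** The point holds as a mismatch between outcome and test, with an unsettled role for the post hoc contrasts. It does not hold as a demonstrated inflation of alpha. With the group effect as sole criterion the false-positive rate is about 5%, and the cost falls on power: about 45% against about 93% for the adjusted day-30 contrast under compound symmetry (47% against 80% under AR(1)), at an assumed 0.5 SD effect at both visits, correlation 0.7 and 48 per group. The rate of about 8–14% is an upper scenario at correlation 0.7. It requires unadjusted tests and a rule, which the protocol does not contain, that any of them may count. The point is worth correcting because the contrast is badly matched to the outcome in the text itself and the data for a better one are already collected.

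**What to change.** - **2.9 and 2.13.1:** name one deciding contrast for platelet aggregation rate, the between-group difference at day 30 (end of the 30-day treatment) adjusted for baseline, at 2-sided 0.05.
- **2.13:** state that day 14 and all other post hoc group and time-point comparisons are supportive and cannot by themselves carry an efficacy claim. If a claim at both visits is wanted, test day 14 only if day 30 is significant; this fixed sequence costs no alpha.
- **2.11:** restate the calculation for that contrast, with the SD, the scale of the 14% difference and the same sidedness as 2.13. At present the two sections differ; on 2.11's own inputs, moving to 2-sided 0.05 gives power Φ(2.487 − 1.960) ≈ 70%.

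**Cost:** no new data or visits. The sample-size calculation must be redone, and whether 48 per group suffices cannot be judged until an SD is given. An effect seen only at day 14 could no longer be claimed as a positive primary result.
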